## Assignment of interventions

### Sequence generation

Participants will be randomly allocated using a 1:1 ratio to (1) time-intensive CBT (IN-CBT) or (2) standard weekly CBT (i.e. treatment as usual). Participants in either allocation group will receive treatment delivered by a high-intensity cognitive behaviour therapist (HI CBT therapist). Randomisation will be conducted via an independent online system based at the King’s Clinical Trials Unit (King’s CTU) based at King’s College London. Random allocation will be at the level of the individual participant and minimisation will be used to achieve balance amongst minimisation factors; disorder (OCD, panic, PTSD, social phobia) and site (Croydon, Lambeth, Lewisham, Southwark).

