### Measures related to secondary objectives

#### Initial clinician interview collected at baseline

*Structured clinical interview for DSM-V* (SCID-V [33];). This semi-structured interview is used by clinicians to establish DSM-V diagnoses, which will be part of initial screening for inclusion in the trial [34].

Routinely collected IAPT data collected at baseline, each clinical session and 3 months postpartum:
*Demographic* (at baseline only)—maternal age, ethnicity, occupation, relationship status, whether they are taking psychotropic medication and pregnancy stage will be recorded.**GAD-7* [35] is a well validated and widely used 7 item measure of anxiety and a key IAPT outcome measure used routinely. A change of 4 or more on the GAD has been found to be clinically significant across anxiety disorders [36]. *This is the potential primary outcome measure for a future evaluation trial.*PHQ-9* [37] is a well-validated 9-item questionnaire used to measure symptoms of depression. It is also a key IAPT outcome measure.The *Work and Social Adjustment Scale* [38] is a 5-item patient self-report measure, which assesses the impact of a person’s mental health difficulties on their ability to function in terms of work, home management, social leisure, private leisure and personal or family relationships.Disorder specific measures: one of the following will be used depending on primary disorder.OCD: Obsessive Compulsive Inventory-Revised (OCI [39];). This is a 42-item self-report inventory concerning symptoms of OCD. The internal consistency for the full scale is high (0.86–0.95). The OCI also shows good discriminative validity and is reliable to measure change in symptoms over time.Panic: Mobility Inventory (alone) [40]. This self-report scale requires respondents to rate avoidance of a range of specific situations over the last week on a scale of 0–4. The inventory has good reliability, validity and sensitivity to change.PTSD: Impact of Events Scale (IES [41]). This is a 22 item self-report scale of symptoms of PTSD. The scale has excellent internal consistency [42].Social Phobia: The Social Phobia Inventory (SPIN [43]) has 17 items and a cut-off score of 19 or above. For each item, respondents rate from 0 to 4 how bothered they have been by the item during the past week. The total score provides a measure of the severity of social phobia and the item has good sensitivity to change.

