### Outcome progression criteria

Primary feasibility outcomes:
(i)if it is possible to identify/recruit patients via (a) information provided in healthcare settings at booking visits/by midwives/self-referral and (b) approach by a primary care therapist. We require a minimum of 30% of those approached to be eligible participants from each recruitment method for each to be deemed feasible. An acceptable recruitment rate (number of consented participants) would be at least 3 participants/month(ii)If participants are willing to be randomised. We require that 70% of eligible participants are randomised to be deemed feasible(iii)If the intervention is received as intended in both arms using a fidelity content checklist. A minimum of 70% of participants in the trial would need to complete > 60% of each intervention in hours for each to be deemed feasible, i.e. 7.2 h out of 12 [28]. For completers in the intensive arm, these treatment hours will need to be completed in the 2-week window(iv)Acceptability of both interventions to participants will be determined by qualitative investigation enquiring about experiences and positive and any negative effects of all aspects of treatment, and a 3-point rating scale to assess how useful the treatment was for anxiety and parenting(v)Establishing the parameters needed in order to estimate the sample size for a full trial. For example, standard deviation of the potential primary outcome measure GAD-7(vi)Participation and data completion at 3m outcome assessment; a follow up rate of > 70% is required to determine feasibility(vii)The acceptability of assessment measures to participants; this will be determined by qualitative interview and brief 3-point rating scales asking if it was acceptable and clear

Secondary clinical outcome measures:
(i)Clinical outcome measures for depression, anxiety, overall functioning and anxiety disorder symptoms collected at 3 months postpartum(ii)Health service use at 3 months postpartum

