### Sample size estimation

In line with guidance on feasibility studies, no power calculation has been carried out [55]. A sample size of 30 in each intervention group has been recommended to answer questions relating to feasibility [56, 57].

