#### Questionnaire data

Questionnaire data will be collected via weblink using existing data collection methods in IAPT services and/or hard copies as preferred, completed in participants own time. Initial clinician interviews will be conducted over the phone at a suitable time for the mother, or in person if she prefers. IAPT measures are routinely collected at each contact so collecting this treatment data will not involve additional burden for women.

All outcomes will be summarized at 3 months postpartum; video and qualitative interview audio data will be collected during a visit to the participant’s home (or remotely) at this point in addition to the IAPT measures.

As per standard practice in IAPT services, anxiety, depression and disorder-specific measures will be taken at each point of contact. Participants will be asked to complete the additional measures at the baseline and outcome points.

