### Statistical methods

#### Quantitative data

Quantitative data analysis will be primarily descriptive to aid the planning of a future RCT. Participant flow through the study will be presented following CONSORT guidelines. Descriptive data will be presented in the form of means and standard deviations; medians and ranges; or percentages with 95% confidence intervals, as appropriate depending on the data being described.

The following feasibility parameters will be calculated: (1) percentage of participants meeting eligibility criteria (those eligible/those approached or referred) by recruitment channel into the study; (2) number of participants recruited per month (defined as those consented); (3) percentage of individuals consenting to randomisation (those randomised/those consented); (4) percentage of participants completing treatment in each arm (number of participants receiving adequate treatment dose, defined as 60% of treatment hours/those randomised); (5) percentage completing the outcome measures at 3m postpartum (number of participants completed at least one follow-up measure/those randomised); (6) between group pre-post effect sizes and confidence intervals, adjusting for randomisation stratifiers (fixed effect) and therapist (random effect), and variance on the potential primary outcome measure at 3 months post-randomisation; (7) summary statistics on acceptability of intervention and outcome measures measured using a 3-point Likert scale. Data will be presented overall and subgroup summaries by disorder.

Descriptive data on therapist competence and compliance will be presented using standardised Cognitive Therapy Scale Ratings (CTS-R) and number of treatment elements completed from checklist.

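### The 3-month follow-up rate counts any one completed measure, so the >70% progression criterion can be met while GAD-7 follow-up is 70% or lower

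*Protocol article*

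**What the plan says.** Under Outcome progression criteria, item (vi) reads "Participation and data completion at 3m outcome assessment; a follow up rate of > 70% is required to determine feasibility". The criterion does not say what makes a woman count as followed up. The only formula is item (5) of the feasibility parameters under Statistical methods, Quantitative data: the "percentage completing the outcome measures at 3m postpartum (number of participants completed at least one follow-up measure/those randomised".

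Table 1 lists seven measures at the 3-month postnatal assessment (PHQ-9, GAD-7, WSAS, a disorder-specific measure, PBQ, CARE Index and ADSUS), plus the qualitative interview. They do not all arrive by one route. Questionnaires are completed by weblink or on paper in the woman's own time, whereas "video and qualitative interview audio data will be collected during a visit", in person or remotely.

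Of the GAD-7 the article says: "This is the potential primary outcome measure for a future evaluation trial". Progression criterion (v) asks for sample-size parameters, giving as its example the "standard deviation of the potential primary outcome measure GAD-7". Item (6) of the feasibility parameters asks for effect sizes and variance on the same potential primary outcome. Study aims and objectives says that follow-up rates are among the results that will inform the full trial.

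**The concern.** Criterion (vi) names two things, taking part and completing data. The formula measures only the first. Item (5) is labelled in the plural, as completion of the outcome measures, but its numerator accepts a single one. A woman who returns only the service-use form, or takes part only in the video, counts the same as one with a full set.

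The full trial needs to know what share of randomised women will supply its primary outcome. No progression criterion asks this, so a go decision could rest on a follow-up rate that does not show whether the GAD-7 was obtained. Anyone who carried that rate into a full-trial sample size as the attrition allowance could plan for too few women.

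**Working it through.** **Inputs**

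- Threshold: more than 70% (Outcome progression criteria, item (vi)).
- Numerator and denominator: "number of participants completed at least one follow-up measure/those randomised" (Quantitative data, item (5)).
- Number randomised: 60. This is 2 × 30, from "A sample size of 30 in each intervention group has been recommended to answer questions relating to feasibility" (Sample size estimation) with 1:1 allocation (Sequence generation).
- GAD-7 completeness among women with at least one measure, called c below: not given. Values are assumed, up to 100%.

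The 70% threshold is set by judgement and no power calculation was made, so the plan has no derived figure to reproduce.

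**Step 1: direction.** A woman with a 3-month GAD-7 has, by definition, at least one measure. Hence GAD-7 rate = any-measure rate × c, with c ≤ 1. The stated rate can equal or exceed the GAD-7 rate and can never be below it.

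**Step 2: pass mark.** 42/60 = 70.0%, which is not above 70%. 43/60 = 71.7%, so 43 is the smallest passing count. The rule sets no minimum for the number of GAD-7 values.

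**Step 3: at the pass mark.** GAD-7 values available if 43 women count:

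| Assumed c | Women with GAD-7 | Share of 60 | Criterion as written | Criterion on GAD-7 |
|---|---|---|---|---|
| 100% | 43 | 71.7% | met | met |
| 95% | 41 | 68.3% | met | not met |
| 90% | 39 | 65.0% | met | not met |
| 80% | 34 | 56.7% | met | not met |
| 70% | 30 | 50.0% | met | not met |

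**Step 4: away from the pass mark.** Exact binomial probability of at least 43 out of 60, for an assumed true any-measure rate a and GAD-7 rate a × c:

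| a | As written | GAD-7, c = 90% | GAD-7, c = 80% | GAD-7, c = 70% |
|---|---|---|---|---|
| 75% | 0.78 | 0.30 | 0.04 | <0.01 |
| 80% | 0.96 | 0.59 | 0.13 | 0.01 |
| 85% | 1.00 | 0.85 | 0.32 | 0.04 |
| 90% | 1.00 | 0.97 | 0.59 | 0.10 |

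With c = 100% the two definitions coincide. The true GAD-7 rate exceeds 70% only if c > 0.70/a: 93% at a = 75%, 87.5% at a = 80%, 82% at a = 85% and 78% at a = 90%.

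**Step 5: if the rate were used for attrition.** To obtain n analysable women, a planner would recruit n/(any-measure rate). The number actually analysable is n × GAD-7 rate/any-measure rate = n × c, a shortfall of 1 − c. An assumed 45/60 (75%) against 38/60 (63.3%) gives c = 38/45 = 0.844, a shortfall of 15.6%. With c = 100% the shortfall is zero.

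**Step 6: precision of the GAD-7 SD.** The 95% interval, as a multiple of the estimated SD (chi-square, n − 2 degrees of freedom), is about 0.82 to 1.28 with 43 values and 0.79 to 1.35 with 30. This effect is modest.

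**The case against.** The strongest reply is that the gap may be small. The GAD-7 has seven items, is routine in these services, and is collected with the PHQ-9, WSAS and disorder measure. The 3-month visit is described as additional to those measures, and nothing in the article suggests that many women would give some other measure and omit the GAD-7. This stands as a reason not to assume a large effect. It does not guarantee the value: the last scheduled therapy contact is at 1 month postpartum, so the 3-month GAD-7 falls after therapy sessions have ended, and questionnaires are returned separately from the visit.

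A second reply is that item (6) and the CONSORT flow would show planners how many GAD-7 values exist. Item (6) does need that count, but the count does not enter the progression rule.

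Third, while the primary outcome of the full trial is unsettled, an any-measure rate is a reasonable measure of retention. That holds for the participation half of criterion (vi), but not for the data-completion half. Reporting both rates would expose a gap, but the plan would still have to say which one governs.

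A reader might also infer that this rate fixes the attrition allowance, so that the full trial will be under-sized for an outcome already chosen. The article supports neither step. It says only that follow-up rates inform the full trial, and it calls the GAD-7 the potential primary outcome.

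**Conclusion.** The point holds as a fault in a stated definition. Criterion (vi) concerns data completion, its only formula accepts any one measure, and the criterion can therefore pass with GAD-7 follow-up at or below 70%. At the pass mark of 43 out of 60, one missing GAD-7 among the women counted is enough.

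That conclusion needs only the article's text and a denominator of 60. The practical size cannot be fixed from the article, because it depends on GAD-7 completeness among the women counted. The probabilities in Step 4 and the 16% shortfall in Step 5 are illustrations under assumed values, and the effect vanishes at full completeness. A shortfall in the full trial arises only if the any-measure rate is in fact used to plan attrition.

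**What to change.** Define the rate in item (5), and the rate that governs criterion (vi), as participants with a scoreable GAD-7 at the 3-month postpartum assessment divided by all randomised. Report it overall and by arm. Alongside it, report the any-measure rate, labelled as participation, and completion of each 3-month measure. Use the GAD-7 rate if attrition is later planned for a full trial with that outcome.

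No new data are needed. The cost is a possibly lower rate and a stricter criterion. Since recruitment began in September 2019, this changes a pre-specified go/no-go rule and is more than a wording edit. It should be documented as such, with its reason and date, and made before outcome data are examined.

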### Inclusion criteria

Women must have the following characteristics prior to randomisation:
Aged ≥ 18 yearsPregnant, between 12 and 25 weeks gestationMeet criteria for Diagnostic and Statistical Manual of Mental Disorders Fifth Edition (DSM-V) for OCD, PTSD, social anxiety or panic disorder on the Structured Clinical Interview DSM-V (SCID-V)Eligible for referral to Lambeth, Lewisham, Southwark or Croydon IAPT services (i.e. has local general practitioner, common mental disorder and level of risk manageable within primary care)Available (by self-report) for either IN-CBT or standard weekly treatmentNot taking psychotropic medication or taking stable dose of medication for at least 6 weeksAble to provide informed consent

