### Blinding

For each allocation to the IN-CBT or standard weekly treatment group, the participant, their therapist and the research psychologist will be aware of the allocation. The research assistant will be blind to the group allocation and will not have access to allocation databases. The research assistant will collect outcome measures at baseline, 1 month and 3 months (primary outcome point) and will be blind. They will conduct the qualitative interview last as it will likely lead to unblinding. The senior statistician will be blind to the group allocation until the end of the trial.

The senior statistician will become unblind once the primary and secondary analyses have been performed. The Statistical Analysis Plan will be drafted by the trial statistician and the senior statistician will contribute fully blinded. The outcome assessor will be unblinded at the end of final outcome assessments by conducting the qualitative interview, as the study is not double blind. This occurs after the other assessment information has been collected.

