### Data collection and management

#### Baseline assessment

Baseline measures will be collected by the research psychologist or research assistant prior to the assignment of participants to the intervention groups. Baseline measures will be collected via weblink using existing data collection methods in IAPT services or hard copies as preferred by participants and will be completed in participants own time. Initial clinical interviews will be conducted over the phone at a suitable time for the mother, or in person if she prefers. As per standard practice in IAPT services, anxiety, depression and disorder specific measures will be collected at each point of contact. Participants will be asked to complete the additional measures at the baseline and outcome points. The postnatal follow-up video and qualitative interview (see below for details) will be collected during a visit to the participant’s home by the research assistant who will be blind to the allocation status of the participant. Assessments may take place via phone or video link using Microsoft Teams, depending on current restrictions due to the Coronavirus.

A list of measures collected during the study and the timepoints of data collection are presented in Table 1.

**Table 1 Tab1:** Study measures at each timepoint

Measure	Pre-treatment baseline assessment	After first 2 h of treatment	Late pregnancy follow-up session^a^	3m postnatal outcome assessment
Screening measures				
Structured clinical interview for DSM-V (SCID)	X			
Routinely collected IAPT measures (at every clinical session)				
Demographics	X			
PHQ-9 (Depression)	X		X	X
GAD-7 (Anxiety)	X		X	X
The Work and Social Adjustment Scale (WSAS)	X		X	X
Disorder specific measure (OCI, Panic, IES, SPIN)	X		X	X
Trial specific measures				
Working Alliance Inventory (WAI)		X		
Pregnancy related anxiety questionnaire (PRAQ)	X		X	
Postpartum bonding questionnaire (PBQ)				X
Mother-infant interactions (CARE index)				X
Adult Service Use Measure (ADSUS)				X
Qualitative interview				X

^a^One hour follow-up session with therapist administered during late pregnancy (33–35 weeks gestation)

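### The GAD-7 effect size and variance are set at 3 months post-randomisation, but everywhere else the 3-month outcome, where given an origin, is counted from birth

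*Protocol article*

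**What the plan says.** Parameter (6) in Statistical methods, Quantitative data, covers the between-group effect size with its confidence interval and the "variance on the potential primary outcome measure at 3 months post-randomisation". Outcome progression criteria, item (v), identifies the measure and the purpose: the study is to supply sample size parameters for a full trial, for example the "standard deviation of the potential primary outcome measure GAD-7".

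Elsewhere the outcome is tied to birth:

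- Table 1 (Baseline assessment) has a final column headed "3m postnatal outcome assessment", in which GAD-7 is marked.
- Questionnaire data gives a general rule: "All outcomes will be summarized at 3 months postpartum".
- Measures related to secondary objectives lists the routine measures, GAD-7 included, at baseline, at each clinical session and at 3 months postpartum.
- The secondary clinical outcomes under Outcome progression criteria are placed at 3 months postpartum.
- Parameter (5), directly before parameter (6), measures completion at 3 months postpartum.

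The Blinding section gives a schedule with no origin: "The research assistant will collect outcome measures at baseline, 1 month and 3 months (primary outcome point) and will be blind". Table 1 has no 1-month column. The only other 1-month contact is the therapist follow-up session at 1 month postpartum, described for both arms.

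**The concern.** Two adjacent items in one list count the same three months from different events, and one of them has no visit behind it. Parameter (6) is the only listed analysis that yields the GAD-7 variance and effect size, and estimating sample size parameters is part of the study's primary objective.

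A statistician following the text literally would have to assemble GAD-7 scores from around week 13 after randomisation, mostly from pregnancy. The resulting standard deviation and effect size would describe a different period from the postnatal assessment that the rest of the document treats as the outcome. While both anchors stand, the time point can also be chosen after the data are seen. The Blinding section does not settle the matter, because its 3-month primary outcome point could be read either way.

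**Working it through.** The plan states no interval between randomisation and the final assessment, so there is no figure of its own to reproduce. The check is calendar arithmetic.

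**Inputs**

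- Gestation at randomisation, r: 12 to 25 weeks. This is from Inclusion criteria, introduced by "Women must have the following characteristics prior to randomisation".
- Three months: 365.25/12 × 3/7 = 13.04 weeks, taken as 13.
- Gestation at birth, b: not given in the document. I assume 40 weeks and show 37 to 42 as a range.
- Late-pregnancy session with GAD-7: 33 to 35 weeks' gestation (Table 1 footnote).

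**Step 1. Where 3 months post-randomisation falls: r + 13**

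- r = 12: 12 + 13 = 25 weeks' gestation.
- r = 25: 25 + 13 = 38 weeks' gestation.

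This is before birth at 40 weeks for every eligible woman. Only late randomisation combined with early birth would put it after delivery.

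**Step 2. Weeks from randomisation to 3 months postpartum: (b − r) + 13**

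| Birth at | r = 25 | r = 12 |
|---|---|---|
| 37 weeks | 12 + 13 = 25 | 25 + 13 = 38 |
| 40 weeks | 15 + 13 = 28 | 28 + 13 = 41 |
| 42 weeks | 17 + 13 = 30 | 30 + 13 = 43 |

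The interval is 28 to 41 weeks for birth at 40 weeks, and 25 to 43 weeks across births at 37 to 42 weeks.

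**Step 3. Distance between the two time points: [(b − r) + 13] − 13 = b − r**

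The gap is simply the time from randomisation to birth. For birth at 40 weeks it is 15 to 28 weeks; across 37 to 42 weeks it is 12 to 30 weeks. The shortest interval in Step 2, 25 weeks, is about twice the stated 13, so the two readings cannot coincide for a term birth.

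**Step 4. Whether an existing visit could stand for 3 months post-randomisation**

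The late-pregnancy session falls between 33 − 25 = 8 and 35 − 12 = 23 weeks after randomisation. It can be at 13 weeks only if r lies between 33 − 13 = 20 and 35 − 13 = 22 weeks. It serves for some women but not for the trial as a whole. GAD-7 is also taken at every clinical session, but those sessions follow treatment and are not fixed in time from randomisation. Table 1 has no column timed from randomisation.

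**The case against.** The strongest reply is that this is one wrong word and the document corrects it. The Questionnaire data section states a general rule, and Table 1, the measures section, the secondary outcomes and parameter (5) all agree with it. GAD-7 is scheduled at 3 months postnatal whatever parameter (6) says, so no data are lost. The study is a feasibility trial with no power calculation and mainly descriptive analysis. All of this stands. It limits the consequence and shows which way the correction should go. It does not make the sentence right, and that sentence governs the estimate the definitive trial will use.

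A reader might go further and infer that no GAD-7 data would exist at 3 months after randomisation, or that scores would be largely missing in the intensive arm and present in the weekly arm. The document does not support either inference:

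- Scores are collected at every clinical session and at a late-pregnancy session offered in both arms.
- Weekly treatment is 8 to 10 hours at one hour a week. If started promptly, it could be over by week 13.
- Intensive treatment lasts 1 to 2 weeks but may be delivered at any point from 12 to 36 weeks of pregnancy, so it need not have ended long before.

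Availability might differ by arm, but nothing allows the size of a difference to be stated. Nor does the use of therapist contacts add a distinct blinding problem: GAD-7 is self-reported, and participants know their allocation at every time point, including postpartum.

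The Blinding schedule can fairly be read as postpartum, since a 1-month postpartum session exists and routine measures are taken at every session. What remains is that a blinded research assistant is said to collect outcomes at 1 month, while Table 1 shows no such assessment and the known 1-month contact is with the therapist. This is a secondary inconsistency and does not bear on parameter (6).

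**Conclusion.** The point holds as a contradiction in the stated time point of the GAD-7 effect size and variance. Parameter (6) counts from randomisation, and every other place that gives the 3-month outcome an origin counts from birth. The two times are 15 to 28 weeks apart if birth is at 40 weeks, and 12 to 30 weeks apart for births at 37 to 42 weeks. The gestation at birth is my assumption; the randomisation window is the document's.

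Taken literally, parameter (6) would estimate the sample size inputs from scores that happen to fall near 13 weeks after randomisation, mainly in pregnancy, possibly with different availability by arm. That last possibility cannot be quantified and should not be presented as established. The likely explanation is a drafting slip. It should still be corrected before analysis, because it fixes the wrong time for the estimate that progression criterion (v) relies on.

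**What to change.** In parameter (6), replace post-randomisation with postpartum, so that it matches parameter (5), Table 1 and the general rule in Questionnaire data.

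In the Blinding section, state that the 3-month point is postpartum. Reconcile the 1-month outcome collection with Table 1: either delete it, or add it to the table with its origin and the person who collects it.

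The correction to parameter (6) and the 3-month anchor are wording only and need no new data. The 1-month item is also wording, unless the team confirms that a separate blinded 1-month assessment was intended. An assessment window and a summary of time from randomisation by arm would be useful, but they commonly belong in the statistical analysis plan, and their absence here is not part of this point.
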